#### Functional assessment of Cancer therapy – Breast (FACT-B)

The FACT-B [41] is a 44-item scale designed to measure multidimensional quality of life in breast cancer patients. The FACT-B has demonstrated acceptable reliability (Cronbach’s alpha of 0.90) and concurrent validity (0.87 correlation with the Functional Living Index-Cancer and 0.86 correlation with the Functional Assessment of Cancer Therapy-General).

#### Brief COPE

The Brief Cope [42] is a 28-item scale designed to assess a wide range of coping responses. The Brief COPE has been used in studies of cancer patients and demonstrates good reliability and validity.

#### Pain – Frequency, Intensity, and Burden Scale (P-FIBS)

The P-FIBS [43] is a 4-item scale that assesses the frequency, intensity, and burden of pain.

#### Dimensional Anhedonia Rating Scale (DARS)

The DARS [44] is a 21-item scale that assesses anhedonia.

#### Anthropomorphic assessments

Height will be assessed at baseline. Weight and waist circumference will be measured at each assessment time point. Height and weight measurements will be used to calculate Body Mass Index (BMI).

#### Metabolic indices

Blood samples will be collected by a trained phlebotomist to allow for evaluation of markers of metabolic health, including blood glucose, triglycerides, and lipids.

#### Relationship status

A single-item question will ask participants to indicate their current relationship status from one of 7 categories (single, never married; cohabiting with partner; married, living together; married, not living together; separated; divorced; widowed). The Couples Satisfaction Index (CSI) [45] is a 16-item form that captures relationship quality among participants who endorsed currently being in a romantic relationship. The CSI is a well-validated and reliable measure that draws from other previously established relationship satisfaction measures.

#### Physical activity stages of change questionnaire

The 4-item scale assesses the current stage within the Transtheoretical Model framework (Pre-contemplation, Contemplation, Preparation, Action, Maintenance). These stages are highly correlated with change in physical activity over time [46].

#### Physical activity self-efficacy questionnaire

The 5-item scale assesses self-efficacy for physical activity. Activity-specific self-efficacy is highly correlated with activity change and psychosocial outcomes [46].

## Statistical analysis

The goal of identifying the most effective components of physical activity intervention will be accomplished through the MOST design in which the four interventions (supervised exercise, facility access, self-monitoring, and active living counseling) each at two levels (presence, absence) are included for a total of 16 combinations (see Table 1). The 500 participants will be divided into one of the 16 combinations for about 31 participants per combination. Note that some participants receive more than one intervention so that half the sample (*n* = 250) receives each intervention. All participants completing baseline and at least one post-baseline assessment will be used in the analysis.

To accomplish the analytical goals, a linear mixed-effects model (using SAS Proc Mixed), will be conducted with MVPA as the outcome and with time (3 months and 6 months) as the within-subjects factor and intervention (i.e., supervised exercise, facility access, self-monitoring, and active living counseling) as the between subjects factor, along with all two-way interactions. Baseline minutes of MVPA, age, BMI, race/ethnicity, socioeconomic status, and education will be included as covariates, along with other relevant demographic and clinical characteristics (e.g., disease stage, treatment, time since diagnosis) collected through participant self-report and data available through the UT Southwestern Cancer Registry. The model will allow for random intercepts while all other factors will be fixed effects.

If MVPA is not sufficiently normally distributed, a log transformation will be used. If the log transformation does not sufficiently normalize the data then non-parametric methods or non-linear models will be considered. As recommended in Collins, et al [47–49], effect coding (− 1, 1) of the interventions will be used instead of dummy coding (0, 1). Main effects and interactions will be estimated for the 3 month and 6 month assessments. Effects will be considered significant if p < = 0.05. The goodness of fit of the final model will be assessed.

This model allows an evaluation of overall pre- post-results for participants, along with more sophisticated analyses of which interventional components are most effective. The results of the analysis will be used to determine which of the intervention components should be included in an intervention package to improve physical activity in breast cancer survivors. However, determining which interventions to include in the intervention package is not straightforward in the presence of large interaction effects. Therefore, interventions will be selected according to the hierarchical ordering principle and modified heredity principle as described in Collins, et al [47–49]. Similar analyses will be conducted to examine changes in secondary outcomes including: quality of life (FACT-B), fatigue (BFI), sleep quality (PSQI), and depressive symptoms (QIDS-SR).

To assess psychosocial factors as predictors and moderators of physical activity behavior change, the linear mixed model repeated measures analysis described above for MVPA will be repeated with each psychosocial factor added as a baseline covariate, in an interaction with intervention group, and in a three-way interaction with intervention group and time. A significant baseline covariate effect in the absence of interaction effects will identify the factor as a predictor of behavior change irrespective of intervention while a significant interaction effect will identify the psychosocial factor as a moderator of behavior change. In other words, the effect of the psychosocial factor varies depending on the intervention. Effects will be considered significant if p < = 0.05.

Analyses related to Goal 3 focus on assessment of factors that will influence future dissemination and implementation of the PACES program. We have selected two important outcomes: 1) program acceptability, and 2) program satisfaction outcomes. These outcomes will be analyzed using the same model described above for MVPA.

The single-site approach used for the analyses despite the accrual from the Cancer Center’s two locations (UT Southwestern Center and Parkland) reflects the fact that the intervention will only be delivered at one site, as survivors from both UT Southwestern and Parkland clinics will complete all study procedures at UT Southwestern Medical Center. Differences in patient populations of the two clinics and within each clinic will be accounted for by including race/ethnicity, socioeconomic status, and education as covariates in the analysis. As described above, we will also utilize “clinic” as a stratification factor in the randomization scheme.

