### Power analysis

We assume a sample of 500, (one cluster based on single-site setting), testing 4 interventions in a full factorial design (16 groups), and testing of main effects and 2-way interactions. Also, we assume a baseline measure of the outcome to be used as a covariate and a correlation between pre- and post-measures of 0.65 (as assumed in Dziak, Nahum-Shani, and Collins [50]). Given a sample size of 500, a main effect of size 0.191 can be detected with 80% power and an interaction effect of 0.382 can be detected with 80% power. Thus, with a sample size of 500 we can detect small main effects (less than 0.2) and interaction effects that are between small and moderate (0.2 to 0.5) [51].

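### The only covariance term named is a random intercept, which under the default residual assumes equal MVPA variance at 3 and 6 months although effects are to be estimated at each visit

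*Protocol article*

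**What the plan says.** The primary analysis in the protocol article (Statistical analysis) is a linear mixed-effects model for MVPA in SAS Proc Mixed, "with time (3 months and 6 months) as the within-subjects factor". Baseline MVPA enters as a covariate, so each woman contributes at most two outcome values. The sole statement on covariance is "The model will allow for random intercepts while all other factors will be fixed effects". No visit-specific residual variance, unstructured covariance or robust standard error is named. On what will be reported, the section says "Main effects and interactions will be estimated for the 3 month and 6 month assessments", and on the threshold, "Effects will be considered significant if p < = 0.05".

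Two further provisions bear on the point. A log transformation is held in reserve, triggered by insufficient normality. The fit of the final model is to be assessed, with no criterion and no alternative covariance given. No SD of MVPA is given for either visit.

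**The concern.** A random intercept plus one residual variance is compound symmetry: one marginal variance shared by both visits and one covariance. A component effect at 6 months is then tested with a variance pooled over 3 and 6 months, and the same holds at 3 months. If the spread of MVPA differs between visits, the standard error is too small at the more variable visit and too large at the other. The effect estimates are not at issue. What is at stake is the error rate and power of the visit-specific tests that the plan promises.

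**Working it through.** **Inputs from the documents.** Total sample 500; each component is compared 250 against 250 ("half the sample (*n* = 250) receives each intervention"); "a correlation between pre- and post-measures of 0.65"; threshold 0.05. Sidedness is not stated, but a two-sided test reproduces the power figure. **Assumed input:** q, the ratio of the larger to the smaller covariate-adjusted SD across the two visits.

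**Step 1: reproduce the plan's own figure.** The Power analysis section states that "a main effect of size 0.191 can be detected with 80% power and an interaction effect of 0.382 can be detected with 80% power". With baseline as covariate, the detectable main effect is (1.960 + 0.842) × √(1 − 0.65²) × 2/√500 = 2.802 × 0.760 × 0.0894 = 0.190. The noncentral t version gives 0.191. Twice that is 0.382, the stated interaction effect. The power figure stands.

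**Step 2: standard errors under a pooled variance.** Set the smaller SD to 1 and the larger to q. With complete data the common variance is v = (1 + q²)/2. Model SE divided by true SE is then √v at the less variable visit and √v/q at the more variable one. With k for either ratio, the true error of the nominal 5% test is 2 × [1 − Φ(1.96k)].

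For q = 1.2: v = (1 + 1.44)/2 = 1.22 and √v = 1.105, so k = 1.105 and 1.105/1.2 = 0.920. The errors are 2 × [1 − Φ(2.165)] = 3.0% and 2 × [1 − Φ(1.804)] = 7.1%.

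| SD ratio q (assumed) | k, less variable visit | True error | k, more variable visit | True error |
|---|---|---|---|---|
| 1.0 | 1.00 | 5.0% | 1.00 | 5.0% |
| 1.1 | 1.05 | 3.9% | 0.96 | 6.1% |
| 1.2 | 1.10 | 3.0% | 0.92 | 7.1% |
| 1.3 | 1.16 | 2.3% | 0.89 | 8.0% |
| 1.5 | 1.27 | 1.3% | 0.85 | 9.6% |

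**Step 3: power.** For a visit-specific effect of 0.191 in units of that visit's own SD, λ = 0.191/(2 × 0.760/√500) = 2.81 and power is 1 − Φ(1.96k − λ). This is 0.80 at q = 1.0. At q = 1.2 it is 0.74 at the less variable visit and 0.84 at the more variable one; at q = 1.5 it is 0.62 and 0.87.

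**Step 4: what is not affected.** Let c be the covariance between visits. The true variance of the two-visit average is (1 + q² + 2c)/4. The pooled model gives (2v + 2c)/4, which is the same because 2v = 1 + q². For the difference between visits, 1 + q² − 2c equals 2v − 2c. With complete data, the time-averaged effect and the component-by-time contrast are therefore tested correctly. Only the effect at a single visit is not.

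**Step 5: simulation.** 3,000 data sets with 16 × 31 = 496 women and an assumed residual correlation of 0.6 gave the following type I errors.

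- Random-intercept model, complete data (less/more variable visit): 0.029/0.075 at q = 1.2 and 0.012/0.087 at q = 1.5.
- Same model with 20% missing at 6 months, taken as the more variable visit: 0.034/0.074 and 0.017/0.102.
- Time-averaged main effect: 0.044 to 0.049 with complete data, 0.052 to 0.060 with 20% missing.
- Unstructured 2×2 covariance, complete data: 0.051/0.049 at q = 1.2 and 0.047/0.038 at q = 1.5.

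Simulation error is about √(0.05 × 0.95/3000) = 0.004. The 0.038 is somewhat low, as is 0.087 against the formula's 0.096 in the same runs. The unstructured fit was not run with missing data.

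**The case against.** The strongest reply is that the article does not fix the residual structure. It says that random intercepts are allowed for, and a random intercept with a separate residual variance per visit is an ordinary Proc Mixed model that fits that sentence. A statistical analysis plan, not shown here, may specify it. This stands: a reader might infer that the plan rules out unequal variances, but the text supports only that it names one covariance element and that the software default then gives equal variances.

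Second, q is pure assumption. That also stands. A reader might look for support in the intervention schedules and infer that components stop between the visits. The documents do not show this. Supervised sessions are described for weeks 1 to 6, before the week 13 assessment. Facility membership lasts 6 months and self-monitoring has no stated end. The 12 bi-weekly classes end near week 6 or near week 24, depending on how the term is read. If skewness links spread to the mean, the log transformation may reduce the difference, but its stated trigger is non-normality, not unequal variance by visit.

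Third, error is mostly moved between visits, not added: the two rates sum to 10.0%, 10.1% and 10.3% at ratios of 1.1, 1.2 and 1.3, against 10% nominal. This is correct, but it does not help someone reading one visit's p-value.

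**Conclusion.** The point holds as a minor, conditional one. Under the plain reading with the default residual, a visit-specific test at nominal 5% has a true error of about 6% to 8% at the more variable visit and 4% to 2% at the less variable one for SD ratios of 1.1 to 1.3. Nothing is lost if the variances are equal. The figures assume complete data, a two-sided test and an SD ratio that the documents do not supply.

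A reader might go further and infer that the wrong components would be chosen for the package. The documents do not support that. The article says selection follows the hierarchical ordering and modified heredity principles and does not say that it rests on visit-specific p-values. Time-averaged main effects stay near nominal. So do component-by-component terms, provided no three-way term with time is fitted; the primary model lists two-way interactions only.

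**What to change.** State the covariance explicitly: an unstructured 2×2 within-person covariance for the 3- and 6-month values, in place of the random intercept (REPEATED time / SUBJECT=id TYPE=UN, with Kenward-Roger degrees of freedom). Alternatively, keep the random intercept and add a separate residual variance for each visit. The two are equivalent when the within-person covariance is positive and no larger than the smaller visit variance. The random intercept should not be combined with TYPE=UN, because the intercept variance could not then be identified.

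The cost is one sentence of text, one SAS statement and one extra parameter (three covariance parameters instead of two) with about 500 women. If the variances turn out equal, almost nothing is lost. The same sentence can cover the other outcomes analysed with this model at both visits.

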## Study interventions

The 500 participants in the physical activity intervention will be randomly assigned to one of sixteen intervention groups (see Table 1).

**Table 1 Tab1:** Randomization schema

Intervention	Group 1	Group 2	Group 3	Group 4	Group 5	Group 6	Group 7	Group 8	Group 9	Group 10	Group 11	Group 12	Group 13	Group 14	Group 15	Group 16
PA education	x	x	x	x	x	x	x	x	x	x	x	x	x	x	x	x
Facility Access		x				x	x	x				x	x	x		x
Supervised Sessions			x			x			x	x		x	x		x	x
Self-monitoring				x			x		x		x	x		x	x	x
Active Living Class					x			x		x	x		x	x	x	x

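### The predictor/moderator model for Aim 2D omits factor × time, and its rule has no place for a psychosocial effect that differs by visit but not by intervention (minor)

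*Protocol article*

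**What the plan says.** The Protocol article, Statistical analysis, defines the base MVPA model with "time (3 months and 6 months) as the within-subjects factor" and the four interventions "as the between subjects factor, along with all two-way interactions". It prescribes −1/+1 effect coding of the interventions and random intercepts only.

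For psychosocial predictors and moderators, the same section repeats this model with each factor entered as a baseline covariate, "in an interaction with intervention group, and in a three-way interaction with intervention group and time". Two rules then classify the factor:

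- Predictor: "A significant baseline covariate effect in the absence of interaction effects will identify the factor as a predictor of behavior change irrespective of intervention".
- Moderator: "a significant interaction effect will identify the psychosocial factor as a moderator of behavior change". The text explains this as meaning that "the effect of the psychosocial factor varies depending on the intervention".

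The term intervention group is not tied to a coding in that paragraph. Elsewhere, under Study interventions, participants "will be randomly assigned to one of sixteen intervention groups".

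**The concern.** The planned three-way interaction has three lower-order two-way terms. Intervention × time is in the base model and factor × intervention is named as an addition. Factor × time is neither. The phrase about all two-way interactions is attached to time and the four interventions. It does not naturally cover the factor, because the later paragraph names factor × intervention separately.

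The model is therefore non-hierarchical, and the decision rule has only two categories. Consider a factor whose effect on MVPA changes between 3 and 6 months in the same way under every intervention. It has no correct label. It may be called a moderator, or its change over time may go unseen. At stake is how Aim 2D sorts psychosocial factors, and so what is later said about who benefits from which component.

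**Working it through.** **The plan's own figures.** The Power analysis assumes N = 500 and a pre-post correlation of 0.65. The residual SD is √(1 − 0.65²) = 0.760. The detectable main effect is 2 × (1.960 + 0.842) × 0.760 / √500 = 0.190 (0.191 with the t distribution), and doubling gives 0.381 to 0.382. Both stated values, 0.191 and 0.382, are reproduced. The article gives no figure for the predictor/moderator analysis, so what follows rests on added assumptions.

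**Assumptions.** Standardised factor and outcome, complete data, no true moderation, factor effect zero at 3 months and δ SD per SD at 6 months. The correlation between 3 and 6 months is also taken as 0.65; the article gives 0.65 only for pre against post.

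**Variances given baseline.**
- Partial correlation of the two visits: (0.65 − 0.4225) / 0.5775 = 0.394.
- 6-minus-3-month difference: 2 × 0.5775 × (1 − 0.394) = 0.70.
- Average of the two visits: 0.5775 × (1 + 0.394) / 2 = 0.4025.

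**Reading 1: 16-level group.** Without factor × time, the three-way term tests whether all 16 slope changes are zero (16 df). With it, the term tests whether they are equal (15 df), which is moderation. The noncentrality is 500 × δ² / 0.70, and the error df on the difference are 500 − 32 = 468.

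| δ | Noncentrality | False moderator, formula | Simulation (3,000 runs) | With factor × time added |
|---|---|---|---|---|
| 0.10 | 7.1 | 30% | 28% | 5% |
| 0.15 | 16.1 | 69% | 66% | 5% |
| 0.20 | 28.6 | 94% | 94% | 4% |

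A second simulation (1,500 runs per setting) used a within-person correlation of 0.5 and no baseline adjustment, so the variance of the difference is 1.0. At δ = 0.20 the noncentrality is 500 × 0.04 / 1.0 = 20, and 78% of runs gave a false moderator. Adding the term brought this to about 4 to 5%.

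**Reading 2: four 0/1 components.** In the second simulation at δ = 0.20, at least one of the four three-way terms was significant in 57% of runs, against 15% with no factor effect. A single component declared as a CLASS variable, with no other three-way term in the model, also absorbs factor × time, because its term then spans one slope change per level. With four CLASS components entered together, each is adjusted for the others, which already span factor × time, so this does not arise.

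**Reading 3: four −1/+1 components, as prescribed.** The three-way columns are nearly orthogonal to factor × time. In the second simulation each term was significant in about 5% of runs at δ = 0.20. The chance that at least one of four was significant was 19%, against 18% with no factor effect; four tests at 0.05 give 1 − 0.95⁴ = 18.5%. The omitted term adds essentially nothing.

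Here the factor's average effect is held equal at both visits. Main-effect detection in the second simulation:

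| Slopes at 3 / 6 months | Main effect significant | Factor × time significant, if included |
|---|---|---|
| −0.1 / +0.1 | 5% | 99% |
| 0 / 0.2 | 71% | 99% |
| 0 / 0.3 | 97% | 100% |

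For a small effect, δ = 0.10 under the 0.65 assumptions, the average is 0.05 with standard error √(0.4025 / 500) = 0.0284. The ratio is 1.76 and power is 42%.

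**The case against.** The strongest reply is that the analysis to be repeated is the one just described, with four effect-coded components. A 16-level factor would bring in three- and four-way intervention terms that this model does not contain, and the sixteen groups describe randomization, not analysis. This largely stands. A reader might infer that the plan will mislabel predictors as moderators at rates of 30% to 94%; the documents do not support that as a general statement, because the prescribed coding avoids it. What remains is that the moderator paragraph says intervention group without repeating the coding.

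A second tempting reading is that the missing term cuts the power to find a predictor from 84% to 42%. It does not. The 84% is the power for an effect at 6 months alone (0.10 / 0.034 = 2.94), a different estimand. Adding factor × time leaves the average-effect test essentially unchanged. Testing each visit separately would also double the predictor tests at 0.05. Nor are one-visit predictors generally missed, given the 71% and 97% above. Nothing in the article suggests that effects at the two visits cancel.

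A third reply is that a condensed article need not list every model term, and that naming a three-way interaction commonly implies its lower-order terms. That is fair in general. Here, however, the article enumerates the added terms, names one two-way term and omits the other. Even if factor × time were implied, the stated rule would call a significant factor × time term moderation.

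**Conclusion.** The point holds as a minor one. The listed model lacks one lower-order term, and the classification rule does not separate variation over time from variation by intervention. A substantial false-moderator rate arises only if the interventions are fitted as the 16-level group or in another coding that lets the three-way term absorb factor × time. Its size depends on the assumed effect and correlations. Under the prescribed −1/+1 coding the consequence is narrower: a change in the factor's average effect between visits is neither modelled nor tested, and the factor is missed as a predictor mainly when its effect is small or the two visits' effects cancel. A reader might infer that the trial's main results are at risk; they are not, since the component effects and the choice of intervention package come from the base model.

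**What to change.** Make three changes to the predictor/moderator paragraph of Statistical analysis:

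1. Add psychosocial factor × time to each model.
2. State that the four −1/+1 components of the MVPA model are used in place of the 16-level group.
3. Limit the moderator rule to significant interactions that involve an intervention, and read a significant factor × time term as prediction that varies over time. The predictor rule's condition on interactions should be narrowed in the same way. Without this change, the added term would itself trigger the moderator label.

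The cost is 1 df per model and one or two sentences, with no new data. If predictor effects are also to be tested at each visit, the plan should say how the extra tests are handled.

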## Enrollment and randomization

Potential participants identified through the screening process will be contacted by phone and invited for a baseline assessment. At this baseline visit, study personnel will explain details of the study to potential participants and give them time to read through the informed consent document. Study personnel will then go through the document and answer any questions. Potential participants who choose to provide informed consent and sign the informed consent form will then proceed to the baseline assessment.

Interested cancer survivors will meet with a trained project interventionist and be assessed for safety of engaging in physical activity, following recommendations identified in the ACSM guidelines (described in Section “Study Design” [14];). The Physical Activity Readiness Questionnaire (PAR-Q) [21] is a self-report questionnaire designed to assess safety of engaging in physical activity. Survivors indicating contraindications to physical activity on the PAR-Q will be asked to meet with a project physician to determine safety prior to project enrollment. In addition, lymphedema and pain will be assessed at baseline and throughout the program to ensure participant safety.

After study eligibility has been confirmed, survivors will complete an baseline assessments, which will involve of collection of demographic data, self-report and objective measurement of physical activity, and psychosocial predictors of physical activity behavior change (see Section 6.2.3 for full description of outcome assessments). Baseline physical activity will be measured objectively with an Actigraph GT3X+ accelerometer. Survivors will be asked to wear the Actigraph for a 7-day period and will be scheduled for a randomization visit to be held at the conclusion of this 7-day period.

At the randomization visit, participants will return their Actigraphs and be randomized into an intervention group. Randomization will be stratified by clinical site (UT Southwestern vs. Parkland). The randomization scheme, conducted by the study statistician ([name]), will consist of balanced blocks within each stratum with block sizes varied and randomly permuted. Randomization tables will be uploaded in RedCap and allocation will occur following completion of baseline assessments.

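### Clinic stratifies the randomisation but is not a named model covariate, so tests may be slightly conservative; one fixed effect would correct this

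*Protocol article*

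**What the plan says.** Under Enrollment and randomization the article states: "Randomization will be stratified by clinical site (UT Southwestern vs. Parkland". The scheme "will consist of balanced blocks within each stratum with block sizes varied and randomly permuted". No other stratification factor is named.

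Under Statistical analysis, the primary model is a linear mixed model for MVPA at 3 and 6 months. On covariates: "Baseline minutes of MVPA, age, BMI, race/ethnicity, socioeconomic status, and education will be included as covariates". The list is then left open, with a few examples of what else may enter: "along with other relevant demographic and clinical characteristics (e.g., disease stage, treatment, time since diagnosis". On random effects: "The model will allow for random intercepts while all other factors will be fixed effects". Clinic is in neither list.

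The last paragraph before Power analysis takes up clinic directly. It says that the single-site approach to analysis "reflects the fact that the intervention will only be delivered at one site". It then says: "Differences in patient populations of the two clinics and within each clinic will be accounted for by including race/ethnicity, socioeconomic status, and education". Clinic itself is given a role only at allocation: "we will also utilize “clinic” as a stratification factor in the randomization scheme".

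**The concern.** When allocation is blocked within clinic, each component is close to balanced within each clinic. Any difference in MVPA between the clinics then largely cancels out of the component contrasts. A model without clinic does not know this. It leaves the between-clinic variation in its residual, so the reported standard error is larger than the actual sampling error of the estimate. An analysis that follows the randomisation conditions on the stratifier.

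The reason given does not answer this. Delivery at one site bears on whether outcomes cluster by place of delivery. It does not bear on whether the model should include the factor that restricted the allocation. Race/ethnicity, socioeconomic status and education may absorb much of the difference between the clinics, but nothing ensures that they absorb all of it.

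At stake is a small amount of reported precision for the component effects. The choice carries over, because the article reuses this model for the secondary outcomes, the predictor and moderator analyses, and acceptability and satisfaction.

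**Working it through.** **Inputs from the article.** N = 500, with 250 participants at each level of a component; pre-post correlation 0.65; threshold 0.05 (sidedness not stated, two-sided assumed); detectable main effect 0.191 at 80% power.

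**Inputs not in the article.** The share R² of residual variance that clinic explains after the planned covariates, and the clinic split. Both are assumed below and shown as ranges.

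**1. The plan's own figure.**
- Residual SD after baseline adjustment = √(1 − 0.65²) = 0.760.
- Standard error of a main effect = 0.760 × √(4/500) = 0.0680.
- Power at 0.191 = Φ(0.191/0.0680 − 1.96) = 80.2%, against the stated 80%.

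The figure reproduces, with no clinic term in it.

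**2. With and without clinic.** Under balanced stratified allocation the actual standard error is about 0.0680 × √(1 − R²). A model with clinic reports that value. A model without clinic reports 0.0680.
- Power with clinic = Φ(0.191/[0.0680√(1 − R²)] − 1.96)
- Power without clinic = Φ((0.191 − 1.96 × 0.0680)/[0.0680√(1 − R²)])
- Actual type I error without clinic = 2[1 − Φ(1.96/√(1 − R²))]

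| R² (assumed) | Power without clinic | Power with clinic | Difference (points) | Type I error without clinic |
|---|---|---|---|---|
| 0 | 80.2% | 80.2% | 0 | 5.0% |
| 1% | 80.4% | 80.6% | 0.3 | 4.9% |
| 2% | 80.5% | 81.0% | 0.6 | 4.8% |
| 5% | 80.8% | 82.2% | 1.4 | 4.4% |
| 10% | 81.5% | 84.2% | 2.7 | 3.9% |

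Differences are taken before rounding.

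**3. How large a clinic gap this needs.** With a share q of participants from one clinic, gap = 0.760 × √(R²/[q(1 − q)]) in outcome SD, after all planned adjustment. For splits from 50:50 to 70:30:
- R² = 5% needs a gap of 0.34 to 0.37 SD.
- R² = 10% needs a gap of 0.48 to 0.52 SD.
- A gap equal to the target component effect, 0.191 SD, gives R² = q(1 − q) × (0.191/0.760)² = 1.3% (70:30) to 1.6% (50:50).

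**4. Simulation.** Blocked 2⁴ allocation within two clinics, assumed 70:30 split, one baseline-adjusted outcome, all two-way interactions between components, 3,000 runs per scenario. Here the clinic gap is added on top of the residual, so power without clinic can fall below 80%.

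| Clinic gap (residual SD) | SE without clinic | SE with clinic | Power without clinic | Power with clinic |
|---|---|---|---|---|
| 0.2 | 0.0683 | 0.0680 | 80.9% | 81.2% |
| 0.4 | 0.0692 | 0.0680 | 79.1% | 80.0% |
| 0.6 | 0.0705 | 0.0680 | 78.2% | 80.4% |

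The mean estimates matched between the two models. So did the empirical spread of the estimates: 0.0686 against 0.0685 at a gap of 0.4, and 0.0669 against 0.0668 at 0.6. Omitting clinic therefore inflates the reported standard error and hardly changes the estimator. Type I error without clinic was below 5% in every scenario. At a gap of 0.6 it also ran low with clinic in the model (3.7%), so for type I error I rely on the closed form in step 2.

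**The case against.** The strongest reply is that little is left for clinic to explain. The model adjusts for baseline MVPA, age and BMI, and the article gives disease stage, treatment and time since diagnosis as examples of further covariates. A stable clinic difference in activity is already partly captured by baseline MVPA. The larger losses in the table need an adjusted clinic gap roughly 1.8 to 2.7 times the component effect that the trial is powered to detect. This stands, and it is why the lower rows of the table should not lead the point.

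Two textual replies also have some force. The open-ended covariate wording does not exclude clinic, and the quoted sentence speaks of patient populations and does not claim to cover every clinic effect. But the one paragraph that discusses clinic in the analysis gives the adjustment to three other variables and keeps clinic for allocation. Since the article argues for that choice, it is not a detail left to a fuller document.

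A reader might infer more than the article supports:
- **Bias or false positives.** Omitting clinic does not bias the randomised contrasts, and the error in the tests is conservative. No component would be falsely selected on this account.
- **A material loss of precision or an underpowered trial.** With balance maintained, the true variance of the estimates barely changes. In the closed form, power without clinic does not fall below the stated 80%.
- **Missing data and travel.** One could argue that clinic predicts dropout, or that Parkland participants face a greater travel burden. The article says only that all procedures take place at UT Southwestern. It gives nothing on distance or on attrition by clinic, so neither argument is used here.

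**Conclusion.** The mismatch is plain in the text: clinic is the only named stratifier, it is not a named covariate, and the reason given for handling it through other variables answers a different question. The consequence is limited to standard errors that are slightly too large and tests that are slightly conservative, and it arises only if clinic predicts MVPA beyond the planned covariates.

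The size cannot be fixed from the article. I would plan on the range of 1-2% of residual variance, where less than one power point is at stake, and treat 5% and 10% as upper scenarios. The figures assume two-sided testing, a single baseline-adjusted outcome and balance within clinic that carries into the analysis set. This is a minor point, worth making because the correction costs almost nothing.

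**What to change.** Add clinic (UT Southwestern vs Parkland) as a fixed effect in the primary MVPA model and in the secondary-outcome and moderator models built on it. Keep race/ethnicity, socioeconomic status, education and the other planned covariates. Reword the paragraph on the single-site approach so that the demographic covariates are used in addition to clinic and not in its place, and so that single-site delivery is given only as the reason for not modelling clustering.

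The cost is 1 degree of freedom of about 490. Clinic must already be recorded for the randomisation, so no new data are needed and the sample size of 500 does not change.
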